## Abstract

**Background:**

The worldwide prevalence of dementia is rapidly rising. Alzheimer’s disease (AD), accounts for 70% of cases and has a 10–20-year preclinical period, when brain pathology covertly progresses before cognitive symptoms appear. The 2020 Lancet Commission estimates that 40% of dementia cases could be prevented by modifying lifestyle/medical risk factors. To optimise dementia prevention effectiveness, there is urgent need to identify individuals with preclinical AD for targeted risk reduction. Current preclinical AD tests are too invasive, specialist or costly for population-level assessments. We have developed a new online test, TAS Test, that assesses a range of motor-cognitive functions and has capacity to be delivered at significant scale. TAS Test combines two innovations: using hand movement analysis to detect preclinical AD, and computer-human interface technologies to enable robust ‘self-testing’ data collection. The aims are to validate TAS Test to [1] identify preclinical AD, and [2] predict risk of cognitive decline and AD dementia.

**Methods:**

Aim 1 will be addressed through a cross-sectional study of 500 cognitively healthy older adults, who will complete TAS Test items comprising measures of motor control, processing speed, attention, visuospatial ability, memory and language. TAS Test measures will be compared to a blood-based AD biomarker, phosphorylated tau 181 (p-tau181). Aim 2 will be addressed through a 5-year prospective cohort study of 10,000 older adults. Participants will complete TAS Test annually and subtests of the Cambridge Neuropsychological Test Battery (CANTAB) biennially. 300 participants will undergo in-person clinical assessments. We will use machine learning of motor-cognitive performance on TAS Test to develop an algorithm that classifies preclinical AD risk (p-tau181-defined) and determine the precision to prospectively estimate 5-year risks of cognitive decline and AD.

**Discussion:**

This study will establish the precision of TAS Test to identify preclinical AD and estimate risk of cognitive decline and AD. If accurate, TAS Test will provide a low-cost, accessible enrichment strategy to pre-screen individuals for their likelihood of AD pathology prior to more expensive tests such as blood or imaging biomarkers. This would have wide applications in public health initiatives and clinical trials.

**Trial registration:**

ClinicalTrials.gov Identifier: NCT05194787, 18 January 2022. Retrospectively registered.

**Supplementary Information:**

The online version contains supplementary material available at 10.1186/s12883-022-02772-5.

## Background

The Lancet Commission [1] has described dementia as “*the greatest global challenge for health and social care in the 21st century.*” The progressive brain degeneration and associated loss of cognitive function have devastating effects on quality of life for people with dementia and their families, and enormous economic impacts on health and social care systems. The worldwide prevalence of dementia is rapidly rising, driven by ageing populations, and current figures of 50 million people living with dementia globally are predicted to triple to more than 152 million by 2050 [2].

The World Health Organization’s key strategy to reduce dementia prevalence is through prevention [3]. Research indicates that up to 40% of dementia cases worldwide could be prevented or delayed by addressing modifiable lifestyle and/or medical risk factors such as physical inactivity, smoking and hypertension [1, 2]. To maximise the effectiveness of dementia prevention strategies, we urgently need readily-accessible population-level screening tools – to facilitate targeted interventions for high-risk individuals or those early in the disease course.

The most common cause of dementia is Alzheimer’s disease (AD), that clinically manifests as progressive loss of memory, language and other cognitive functions. The underlying brain pathology is characterised by accumulation of abnormal amyloid beta (Aβ) and phosphorylated tau (p-tau) proteins followed by neurodegeneration. New data show that silent and progressive brain changes occur 10–20 years before cognitive symptoms emerge, with two stages of AD occurring before dementia: preclinical AD and mild cognitive impairment (MCI) [4, 5]. This critical period of preclinical AD, when there are no detectable clinical symptoms, is the optimal time to intervene with targeted dementia prevention interventions early in the disease [1].

Positron emission tomography (PET) brain scans and cerebrospinal fluid (CSF) tests [6] can measure preclinical AD pathology but they are too invasive, specialist or costly to be used at the population level; currently they are only available in a small number of hospitals and rarely in low- and middle-income countries. Standard pen and paper cognitive tests lack sensitivity in preclinical AD [7]. However, over the past 3 years, a range of new blood-based biomarker assays have been developed that can quantify AD pathology with minimal invasiveness, including in the preclinical phase.

One of the most promising blood-based biomarkers is plasma p-tau181, as it has been shown that levels increase across the AD clinical continuum and correlate strongly with CSF and PET measures of AD pathology [8, 9]. Furthermore, antemortem plasma p-tau181 levels 5–8 years before death predict AD brain pathology at post-mortem, including in those with unimpaired cognition [10, 11]. Baseline plasma p-tau 181 levels in individuals with unimpaired cognition (as well as those with impaired cognition) are predictive of prospective cognitive decline and neurodegeneration [12]. In summary, the development of blood-based biomarkers is a major advance towards identifying preclinical AD in clinical and research settings, and plasma p-tau181 is considered both sensitive and specific to AD pathology. However, the practicalities and cost of obtaining a blood sample and accessing highly-specialist analytic equipment limit wide accessibility to most populations around the world, as well as for large-scale population intervention studies. Very few research centres have access to the specialist and expensive highly sensitive analytical infrastructure required to analyse the blood samples and each biomarker test typically costs at least $50–100 USD.

Thus, there remains urgent need for low-cost non-invasive and accessible tests that can pre-screen individuals for their likelihood of AD pathology prior to more specialist and expensive biomarker tests, or simply to identify individuals at higher risk for targeted risk reduction. A population-level screening test for preclinical AD would have wide applications in public health initiatives and clinical trials. Similar to screening programs for other chronic diseases such as diabetes, cancer and heart disease, a test that allows people to identify likely preclinical AD pathology would provide more time to reduce dementia risk before cognitive decline and before the brain degenerates; it would also enable opportunities for early recruitment to clinical trials. This would transform the effectiveness of dementia secondary prevention strategies in reducing dementia incidence.

There is a growing body of research that shows movement analysis is an effective method to identify the preclinical AD phase; several studies have shown that patterns of human movements change in preclinical AD and decline across the AD continuum. For more than a decade, research studies have found that slowed walking, especially when a dual motor-cognitive task was performed, predicted cognitive decline and dementia years later [13, 14]. However, the scalability of detailed gait analysis is limited by the need for wearable sensors, in person measures, or gait laboratories, and there are also substantial risks of falls.

More recently, several different types of studies have provided strong evidence that hand movement analysis is a sensitive biomarker of preclinical AD. First, functional magnetic resonance imaging (MRI) research has revealed that the human posterior cingulate cortex is specifically involved in control of hand movements [15] and this is highly relevant because the posterior cingulate cortex is known to be one of the first areas of the brain to show abnormalities in preclinical AD – in terms of both hypometabolism [16] and Aβ deposition [17]. This new imaging discovery accords with well-established single-unit microelectrode studies in monkeys that show high activity in the posterior cingulate cortex during forelimb self-paced tapping movements via projections to the primary motor cortex [18]. Taken together, these studies provide evidence that hand movement tests can detect the earliest pathological changes associated with preclinical AD.

Further, in a recent study of older adults with preclinical AD (defined by having elevated CSF Aβ indicative of AD, but with unimpaired cognition) Mollica et al. (2019) found that the speed and variability (a measure of rhythm) of simple finger tapping tests on a computer keyboard are abnormal in preclinical AD, and the *degree* of variability correlates with CSF Aβ levels [19]. These findings support earlier studies that determined hand reaction times correlate highly with CSF Aβ biomarker levels in preclinical AD [20] and progressively worsen over the AD continuum [20–22]. Additionally, it has been shown that even with unimpaired cognition ApoE4 carriers have been found to have delayed hand reactions compared to non-carriers, suggesting hand movements deteriorate at the very earliest stages of preclinical AD [20].

Based on this mounting evidence, and the wide accessibility of computers, including among older adults [23], we have devised TAS Test (or ‘Tasmanian Test’^1^), a new 20-minute online platform of digital motor-cognitive tests that are designed to be completed in people’s own homes without any specialist supervision. Specifically, TAS Test collects a range of hand movement data using standard computer cameras, keyboards and mouse-click data. It builds upon our work that found computer vision and other cutting edge artificial intelligence (AI) technologies can accurately measure hand movements using standard computer equipment [24–27], and that hand movements deteriorate with cognitive decline [28, 29].

For the first time, we will use AI video technologies in a health-related test. Similar technologies have already successfully automated cancer screening from static images (eg breast and lung from mammograms and radiographs, respectively), but we will analyse much richer video images, and collect these in the participant’s own home, or preferred remote setting. Our prior research shows that computer vision accurately measures hand movements [24, 25, 27, 30] and TAS Test combines these advanced technologies with hand-movement tests that are known to be affected in preclinical AD [19–22]. Using plasma p-tau181 test results as ground-truth, this novel remote method has high potential to reliably predict preclinical AD risk. In addition, it also includes computerized tests of cognition that are based on principles of other neuropsychological tests. This will allow exploration of motor-cognitive associations and the development of multi-modal predictive algorithms using a range of different types of data.

In this research, we therefore look beyond the current definition of dementia – a clinical syndrome of cognitive decline – to investigate the detection of AD from a new perspective: by focusing on hand movement analysis. This novel approach capitalises on recent discoveries about movement in preclinical AD and learns from historical neurology breakthroughs made by questioning definitions, particularly around the entwined relationship between movement and cognition*.* For example, Parkinson’s disease, defined as a pure movement disorder for almost 200 years, is now recognised as having ‘non-motor’ symptoms (such as loss of sense of smell, depression and cognitive decline) decades before movement decline. This paradigm shift has unlocked a whole new field of Parkinson’s disease research, producing new biomarkers, drugs and screening tools and greatly improving peoples’ quality of life. Similarly, we could transform AD prevention and research by analysing ‘non-cognitive’ brain functions impaired at the earliest stages of pathology.

There are several practical advantages to using hand movement as the core assessment of a population-level test - including the ease with which it translates across other countries, cultures and languages, and the speed and ease of assessment that can be performed while sitting in front of a home computer. With wide accessibility to computers, we envisage that TAS Test may be an inexpensive first-line population-level screening test that can identify high-risk individuals, including those in remote and rural communities, for further evaluation (including with blood biomarkers, where available) and/or risk modification.

### Aims and hypotheses

The aims of the study are to:Develop and validate the optimal TAS Test protocol to detect preclinical AD and,Validate TAS Test to prospectively estimate 5-year risks of cognitive decline and AD.

We hypothesise that, for adults aged 50 years or older, TAS Test will:Detect preclinical AD (defined as positive blood p-tau181, normal cognition) with high sensitivity and specificity.Estimate the 5-year risk of accelerated cognitive decline and dementia with high precision.

## Methods

### Aim 1

To develop and validate the optimal TAS Test protocol to detect preclinical AD.

#### Design

A cross-sectional observational research design will be used to develop TAS Test protocols and validate these against blood biomarker-defined preclinical AD.

#### Setting

Multi-centre recruitments will take place in Australia via established cohort studies at the University of Tasmania and the University of Sydney, aiming for 500 adults aged 50 years old or more. Participants will be assessed online at home (or their own preferred remote setting) or in the University clinical research facilities if they prefer. It is expected that most will complete the tests at home. They will use a laptop computer or desktop computer with a webcam and microphone. Participants who have not already provided a blood sample for their respective studies, will be invited to attend the University clinical research facilities to do so.

#### Participants

The participants will be recruited from the Tasmanian Healthy Brain Project (THBP) [31] at the University of Tasmania (UTAS) (ethics reference H0018265), and The Healthy Brain Ageing (HBA) Program [32] at the University of Sydney (protocol number 2019/271).

The THBP is a National Health and Medical Research Council (NHMRC)-funded, prospective cohort study that evaluates cognitive ageing in older adults who reside in Tasmania, Australia. Between 2010 and 2014, 556 participants aged 50 years and older were recruited (mean age 60 years) and underwent detailed neuropsychological and cognitive assessments, medical screening, and genetic tests at baseline, with detailed (4–6 hours) annual cognitive assessments for 4 years, then biennially.

The HBA is a specialist early intervention clinic and prospective cohort study that has recruited more than 1,000 participants aged 50 years and older (mean age 66 years) who have concerns about their cognition and reside in New South Wales, Australia. All receive detailed annual clinical phenotyping, including neuropsychological and medical assessments.

Participants from THBP and HBA will be invited to take part in the TAS Test study via email invitation or in person at a scheduled study visit. Inclusion criteria: Male and female adults ≥50 years old with unimpaired cognition. Exclusion criterion: Participants with impaired cognition, defined as declining cognitive trajectories measured by CANTAB Paired Associates Learning (PAL) total errors adjusted for age and sex, and a score > 1.5 SD above the mean total errors adjusted [33]. The rationale for excluding participants with impaired cognition is that, in this study, we aim to develop a test that discriminates participants with preclinical AD (unimpaired cognition and positive p-tau181) from those with healthy ageing (unimpaired cognition and negative p-tau181). Participants may withdraw from the study at any time and for any reason without any consequence to their ongoing participation in THBP or HBA. When an individual withdraws from the study, all the information collected to that point will be kept in the database for data analysis or withdrawal analysis.

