### Sample size

#### Aim 1

We estimate that 17% (or 85 individuals) in the cognitively unimpaired THBP & HBA cohorts will have p-tau181 in the preclinical AD range [45]. We have performed ROC curve analysis using open data from Mollica et al. [19]. This showed area under ROC curve (AUC) of 0.75 for a null linear model including age, sex, ApoE4, and years of education, but not finger tapping, to detect p-tau181 positivity in CSF. To develop the multivariable model, power calculation showed the sample size to compare a screening test with an area under the curve (AUC) > 0.90 against the null model would require 60 positive p-tau181 cases and 290 controls. Thus, we will use 350 in the development dataset (expected 60 [17%] preclinical AD cases) and 150 in the validation dataset (expected 25 [17%] preclinical AD cases) to test cut-offs from the development model. The PROBAST tool [46] confirmed these combined development and validation strategies lower the risk of bias.

#### Aim 2

Based on the age distribution of ISLAND participants, we project that 8.6% of participants currently aged 70–74 years (a cohort of ~ 1300 from the 10,000 recruited) will develop dementia, and more than 16% of the 700 participants currently aged 75+ years will develop dementia over the study duration [47, 48]. Thus at least 200 participants will meet diagnostic criteria for dementia or MCI. Our sample size calculation aims to ensure precise estimation of model parameters while minimising potential of overfitting. A sample of 300 including 100 dementia cases would ensure accurate prediction of the outcome proportion (33%) with a targeted confidence interval of 28–38%. To target a mean absolute prediction error (MAPE) < 0.05, as recommended by Riley et al. [49], a sample of 300 would be adequate for up to 6 predictors in a parsimonious, statistically determined risk prediction model.

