### Statistical analysis

#### Aim 1

To develop the TAS test protocol and validate it against p-tau181, data from 350 participants with no cognitive impairment will develop the model. Data from the remaining 150 participants in this validation dataset will determine the model’s sensitivity and specificity in detecting preclinical AD. Replicates of plasma biomarkers will be assessed for outliers and then averaged. Hand-movement data will be summarised for each participant. Participants with unimpaired cognition and mean p-tau181 above a diagnostic cut off will be classified as ‘preclinical AD’. We will use multiple logistic regression to model the associations between movement features and p-tau181 positivity. Covariates may include age, sex, ApoE4 genotype, years of education, and handedness. As a secondary, more agnostic approach, we will use a deep learning approach to discover features in the video and keyboard movement data that map to p-tau181 positivity. To validate the TAS Test multivariable model, we will use cross-validation for model selection to avoid overfitting and bootstrap procedures to estimate model uncertainty. We will independently validate the model using the remaining 150 participants’ data. Receiver Operating Characteristic (ROC) curves will be plotted against the positive p-tau181 cut-off to assess the sensitivity and specificity of movement models to identify the preclinical AD stage. As TAS Test is intended as a screening test, the resulting curves will allow users to make informed choices about sensitivity and specificity that align with their research or health promotion goals.

#### Aim 2

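### Aim 1 pools two differently recruited cohorts and validates on the same mix without naming cohort in the analysis, so pooled associations and AUC could partly reflect source cohort rather than p-tau181

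*Protocol article*

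**What the plan says.** The Setting section under Aim 1 plans multi-centre recruitment, "aiming for 500 adults aged 50 years old or more", with no target per cohort. The Participants section names the two sources:

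- THBP follows cognitive ageing in older Tasmanian residents. It enrolled 556 people in 2010–2014, with a mean age of 60.
- For the other source, "The HBA is a specialist early intervention clinic and prospective cohort study", and it "has recruited more than 1,000 participants aged 50 years and older (mean age 66 years) who have concerns about their cognition". Its participants live in New South Wales.

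Both sources face one inclusion criterion: "Male and female adults ≥50 years old with unimpaired cognition".

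Under Sample size, Aim 1, a single figure of 17% (85 people) is given for those who, "in the cognitively unimpaired THBP & HBA cohorts will have p-tau181 in the preclinical AD range". The null model there (AUC 0.75) contains age, sex, ApoE4 and education. The target for the screening test is an AUC above 0.90.

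Under Statistical analysis, Aim 1, "Covariates may include age, sex, ApoE4 genotype, years of education, and handedness". Source cohort is not named. The section does not say how the 350/150 split is made. It then states: "We will independently validate the model using the remaining 150" participants' data. The sample size section adds that a risk-of-bias tool supported this combination of development and validation.

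**The concern.** The cohorts were assembled differently: one is selected on cognitive concern and the other is not described that way. They also sit in different states and are run by different universities. If p-tau181 positivity differs between them, cohort is associated with the reference standard. If tapping, speech, test setting or equipment differs too, cohort is also associated with the index test. A feature with no relation to p-tau181 inside either cohort would then show one in the pooled data.

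A random held-out part of the same mix carries the same cohort structure, so it would reproduce such an association. The article calls this step independent validation, and for this particular threat it is not. At stake are which movement features are judged informative and whether the reported AUC would carry over to a population-level screen, where the contrast between these two cohorts does not exist.

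**Working it through.** **The plan's own figures.** 0.17 × 500 = 85, 0.17 × 350 = 59.5 and 0.17 × 150 = 25.5, which match the stated 85, 60 and 25. The 60 cases and 290 controls are also attainable. For AUC 0.75 v 0.90 with uncorrelated AUCs, the Hanley–McNeil variance gives 57/276 at 80% power two-sided and exactly 60/290 at 90% power one-sided. The article states no alpha, power or correlation, so those are assumptions. The sample size is not in dispute here.

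**AUC from cohort membership alone.** For a marker that carries only cohort,

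AUC = 0.5 + 0.5 × [P(HBA | positive) − P(HBA | negative)].

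The cohort mix and cohort-specific rates are assumptions; overall positivity is held at the article's 17% (85 positive, 415 negative). With 250 from each cohort:

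| THBP / HBA positivity | Positives in HBA | Negatives in HBA | AUC |
|---|---|---|---|
| 17% / 17% | 42.5/85 = 0.500 | 207.5/415 = 0.500 | 0.50 |
| 12% / 22% | 55/85 = 0.647 | 195/415 = 0.470 | 0.59 |
| 10% / 24% | 60/85 = 0.706 | 190/415 = 0.458 | 0.62 |
| 7% / 27% | 67.5/85 = 0.794 | 182.5/415 = 0.440 | 0.68 |

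The mix matters. Holding THBP at 10%:

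- HBA share 30% (150 people, 50 positive): 0.5 + 0.5 × (50/85 − 100/415) = 0.67.
- HBA share 70% (350 people, 70 positive): 0.5 + 0.5 × (70/85 − 280/415) = 0.57.

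These are the values when the marker identifies cohort perfectly. A feature that identifies it imperfectly gives less.

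**Gain over the null model.** Under a binormal model, an independent cohort signal of AUC 0.62 added to 0.75 gives Φ(√(0.6745² + 0.3055²)) = Φ(0.740) = 0.77.

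**What it would take to reach the target.** With an HBA share of 30% and all 85 positives in HBA (0% v 57%), cohort alone gives 0.5 + 0.5 × (1 − 65/415) = 0.92. Nothing in the article suggests such a contrast.

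**Effect on feature associations.** Simulation: 500 runs, N = 350, 50:50 mix, logistic regression, one normal feature shifted between cohorts and unrelated to p-tau181 within either.

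| Positivity | Shift (SD) | p < 0.05, no cohort term | p < 0.05, cohort term | Pooled AUC | Within-cohort AUC |
|---|---|---|---|---|---|
| 17% / 17% | 1 to 2 | 5% | 5% to 6% | 0.50 | 0.50 |
| 12% / 22% | 1 to 2 | 19% to 43% | 4% | 0.54 to 0.58 | 0.50 |
| 10% / 24% | 1 to 2 | 33% to 72% | 4% to 6% | 0.57 to 0.61 | 0.50 |

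Under unequal positivity the false association is frequent, while the AUC it produces is modest. A cohort term restores the error rate, and comparing positives with negatives inside the same cohort returns the AUC to 0.50.

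**The case against.** The strongest case on the other side is that the article shows neither link. It reports no positivity by cohort and no TAS Test difference by cohort, and with equal positivity there is no bias. Several features also narrow the contrast:

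- Both cohorts must have unimpaired cognition.
- Age, ApoE4 and education are possible covariates, and the covariate list is open.
- All plasma is assayed at one university on one platform.
- Most testing is expected at home, and device data are collected.
- The route straight from video to p-tau181 status is secondary. The main route uses features from tracked hand keypoints, which do not encode the video background.

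Even the direction is unclear. The THBP mean age of 60 dates from 2010–2014, and the study was registered in January 2022, so the apparent gap to HBA's 66 may have closed or reversed. A condensed article may also leave split mechanics and site terms to an analysis plan.

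Most of this stands, and it limits the size of the problem. It does not remove it. Participants are excluded on a declining trajectory together with a poor paired-associates score, so people who joined HBA because of a concern but score normally remain eligible. Some blood may already have been collected within the parent studies, so timing and handling could differ before the common assay. The article also does more than stay silent: it defines the validation set as the remainder of the same pool and calls the validation independent.

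**Conclusion.** The point holds as a conditional weakness in the Aim 1 validation. If both positivity and TAS Test performance differ by cohort, pooled associations and the pooled AUC could partly measure cohort, and the 150-person validation would not reveal it. Under the assumed 50:50 mix and moderate differences (12% v 22% or 10% v 24%), cohort alone is worth an AUC of about 0.59 to 0.62. All cohort-specific rates, mixes and feature shifts are assumptions.

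A reader might infer more: that a model which merely recognises the source cohort will appear to detect p-tau181, or could meet the success target. The documents do not support that. They report neither of the two differences required. Even the 7% v 27% case gives 0.68, below the 0.75 null model, and 0.90 is passed only in an extreme scenario. A reader might also take the contrast as healthy volunteers against patients, but the article describes THBP participants only as older adults living in Tasmania, and both groups must be cognitively unimpaired.

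The practical harm is more likely to be spurious feature associations and a modestly inflated AUC than a false overall success.

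**What to change.** In Statistical analysis, Aim 1:

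1. State that the 350/150 split is stratified by source cohort and p-tau181 status. This also protects the expected 60 and 25 cases.
2. When testing movement-feature associations and comparing with the null model, include cohort in both the null and the full model. Adding it only to the full model would credit the cohort signal to TAS Test.
3. Beside the pooled AUC, report a cohort-stratified AUC that compares positives with negatives from the same cohort. Compute it from a score that does not use cohort, since a deployed screen will have no such variable. Give sensitivity and specificity per cohort as descriptive results.
4. Treat training on one cohort and testing on the other as exploratory only. With 250 per cohort and equal positivity, 0.17 × 250 = 42.5 cases would be available for development, against the 60 the article requires.

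Cohort is known for every participant, so no new data are needed. The cost is precision: about 25 validation cases in total means roughly 12 or 13 per cohort at an even mix and equal positivity. The headline AUC may also come out slightly lower.

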A sub-sample of 300 people will be selected from the main ‘TAS Test Aim 2’ cohort to attend the linked ISLAND Cognitive Clinic; this clinic provides facilities and expertise for gold standard clinical consensus diagnosis in a ‘one-stop’ interdisciplinary clinic where participants will have neuropsychological, and geriatrician or neurologist assessments, MRI brain scans, and ApoE4 tests. To select this cohort of 300 people for further face-to-face assessments from the larger cohort of up to 10,000 participants, we will invite 200 ISLAND participants (randomly selected) from those who have CANTAB scores (at the 48 month test point) indicative of MCI or AD – ie those with learning/working memory or attention cognitive deficits. A further 100 will be selected as age- and sex-matched controls from the Aim 2 participant cohort (using stratified random sampling) that comprises people with CANTAB scores indicative of unimpaired cognition.

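### Aim 1 defines impaired cognition by CANTAB PAL alone, so a person with a recorded MCI diagnosis or a non-memory deficit can be labelled preclinical AD or healthy ageing

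*Protocol article*

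**What the plan says.** Under Methods, Aim 1, Participants, the inclusion criterion is "Male and female adults ≥50 years old with unimpaired cognition". The only operational definition is the single exclusion criterion, which has two parts. The first reads "Participants with impaired cognition, defined as declining cognitive trajectories measured by CANTAB Paired Associates Learning (PAL) total errors adjusted for age and sex". The second is joined to the first and reads "and a score > 1.5 SD above the mean total errors adjusted". The stated reason for it is that the test should separate "preclinical AD (unimpaired cognition and positive p-tau181) from those with healthy ageing (unimpaired cognition and negative p-tau181").

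The same section describes what the two source cohorts already hold. THBP participants "underwent detailed neuropsychological and cognitive assessments, medical screening, and genetic tests at baseline", with assessments of 4–6 hours repeated yearly for four years and every two years after that. HBA is a specialist early intervention clinic and cohort of people "who have concerns about their cognition and reside in New South Wales, Australia"; of these, "All receive detailed annual clinical phenotyping, including neuropsychological and medical assessments".

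Under Statistical analysis, Aim 1, unimpaired cognition plus a mean p-tau181 above the cut-off makes a participant a preclinical AD case. No further cognitive check is described at that stage. The section Further data collected lists cognitive symptoms and neurological diagnoses, but neither is made an Aim 1 eligibility criterion.

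**The concern.** The claim of Aim 1 is detection before impairment. Both outcome classes must therefore contain only unimpaired people, and p-tau181 should be the only thing that separates them. A rule built on one memory task does not secure this. It passes a person whose deficit lies in attention, executive function, language or visuospatial ability, and one whose cohort record already carries a diagnosis of MCI.

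The protocol's own evidence suggests that such people would perform differently on TAS Test. The Background says that hand movements deteriorate with cognitive decline and that reaction times worsen over the AD continuum. The section on video hand movement tests says that low cognitive capacity goes with larger dual-task motor costs. TAS Test also measures processing speed, attention, visuospatial ability and language directly. Impaired participants in either class could therefore shift the sensitivity and specificity reported for the preclinical stage.

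**Working it through.** **1. The plan's own counts.** 0.17 × 500 = 85 cases; 0.17 × 350 = 59.5 (stated as 60); 0.17 × 150 = 25.5 (stated as 25). These reproduce. The concern is about who carries the label and leaves the sample-size arithmetic untouched.

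**2. Who passes the rule.** Exclusion needs a declining PAL trajectory and a PAL score more than 1.5 SD above the mean. Take an HBA member with normal PAL and MCI recorded at the annual assessment. Neither PAL condition is met, so this person is included. If p-tau181 is above the cut-off the label is preclinical AD; if not, healthy ageing. A person with normal PAL and an attention or language deficit follows the same path. Because the two conditions are joined by *and*, poor PAL without documented decline also passes as written.

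**3. Size of the effect on sensitivity (illustration).** The documents give neither the HBA share of the 500 nor the rate of non-memory impairment. Assumed inputs:
- HBA supplies 150 to 350 participants, of whom 5% to 20% are impaired outside memory: 150 × 0.05 = 7.5 to 350 × 0.20 = 70 people.
- 17% to 30% of these are p-tau181 positive: 7.5 × 0.17 = 1.3 to 70 × 0.30 = 21 cases.
- Share of the 85 cases: 1.3/85 = 1.5% to 21/85 = 24.7%.
- Sensitivity is 60% in unimpaired and 85% in impaired cases.

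Reported sensitivity = (1 − s) × 0.60 + s × 0.85, so the shift is s × 0.25. This gives 0.015 × 0.25 = 0.4 points to 0.247 × 0.25 = 6.2 points.

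**4. The opposing effect on specificity.** The same corners leave 7.5 × 0.83 = 6.2 to 70 × 0.70 = 49 impaired people among 500 − 85 = 415 negatives, or 1.5% to 11.8%. Specificity falls by that share times the extra false-positive rate in impaired negatives, which is unknown. If it too were 25 points, the fall would be 0.4 to 3.0 points.

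**5. A second route to the count.** Let m be the proportion of screened people impaired in any domain, Se the sensitivity of the screen and Sp its specificity. The impaired share of those included is m(1 − Se) / [m(1 − Se) + (1 − m)Sp]. Take m = 10% to 30% (assumed).

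| Screen accuracy | Impaired among 500 | Among 85 cases, if spread evenly |
|---|---|---|
| 97/81% (cited for CANTAB, MCI) | 2 to 8 | 0.3 to 1.3 |
| 82/97% (cited for CANTAB, early dementia) | 10 to 37 | 1.7 to 6.3 |
| 30–50% / 93% (assumed for PAL alone) | 28 to 122 | 4.8 to 20.7 |

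The 93% is the normal proportion within a one-sided 1.5 SD limit. The result ranges from negligible to about a quarter of cases, depending on a detection rate that the documents do not give for PAL.

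**6. What a strict any-domain rule would remove.** With four independent, normally distributed domains, the share of normal people beyond 1.5 SD in at least one is 1 − 0.9332⁴ = 24%.

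**The case against.** The strongest points on the other side are these.

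- **The rule has a cited basis.** It rests on the same source that the Aim 2 Participants section uses for sensitivity and specificity of 97/81% and 82/97%. This stands in part. Those figures are stated for CANTAB in classifying MCI and early dementia, not for PAL alone, not by domain, and not for the two-part rule.
- **Sites may apply the inclusion criterion clinically.** A clinic might not invite someone it has diagnosed with MCI. That is possible, but the only definition the protocol gives is the PAL rule.
- **One common test keeps the label the same at both sites.** This stands. The cohort batteries are not shown to be harmonised, and THBP results may be up to two years old. It argues against replacing PAL, not against adding a recorded diagnosis.
- **The shift is small beside sampling error.** With 25 validation cases and sensitivity 60%, the 95% margin is 1.96 × √(0.6 × 0.4/25) = 19 points. This is true, but contamination is a bias in what is being estimated, and more participants would not remove it.

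A reader might infer three stronger things that the documents do not support. First, that the aims contradict each other, because Aim 2 sends "those with learning/working memory or attention cognitive deficits" to the clinic. Aim 2 draws on a different cohort, that phrase selects whom to invite for consensus diagnosis, and Aim 2's own stable or declining label also rests on PAL. Second, that the cohort batteries are comprehensive and decide status much better than PAL. The article calls them detailed, lists no domains and gives no accuracy figure. Third, that PAL is missing from the cohorts because their descriptions do not mention it. An article condenses, and the cohort protocols are not shown.

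**Conclusion.** The point holds as a weakness in the Aim 1 eligibility definition. As written, it lets people with a recorded MCI diagnosis or a non-memory deficit into both outcome classes, although existing cohort data could identify at least some of them. The text shows that this can happen; it does not show that it will, or how often.

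Sensitivity would tend to be overstated by about 0.4 to 6 points, on the assumed HBA share, impairment rate, positivity rate and the 60% and 85% sensitivities. Specificity would tend to be understated by an amount that cannot be fixed. A reader might infer that TAS Test's accuracy will be inflated overall. That does not follow, because the two effects oppose each other and the net effect on the AUC is uncertain. The case for change rests on the validity of the preclinical label and the low cost of protecting it, not on a demonstrated large bias.

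**What to change.** In Methods, Aim 1, Participants, keep the PAL rule and add that anyone with MCI or dementia recorded at the latest THBP or HBA assessment is also treated as impaired. State whether both PAL conditions are required.

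In Statistical analysis, Aim 1, add a sensitivity analysis that repeats the AUC, sensitivity and specificity after excluding participants impaired in any domain of their cohort assessment. Report the number excluded by cohort and by p-tau181 status.

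Do not make an any-domain 1.5 SD cut the eligibility rule. It could remove up to about 24% of cognitively normal people, when 500 are needed from roughly 1,550 (556 in THBP and more than 1,000 in HBA), and it would rest on batteries not shown to be comparable.

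The cost is protocol wording, extraction of data already held, and somewhat fewer eligible participants. Two limits should be stated with the results: THBP assessments may be up to two years old, and the assessments may differ between sites.
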